## Data safety and monitoring plan

Day-to-day safety monitoring will be the responsibility of the study manager. In this she will be assisted by an independent safety officer who will review the blood results, and the fieldworkers performing blood pressure measurements and completing interviews. In the event that the pre-determined safety thresholds are breeched she will alert the study manager, who will contact the clinic staff to ensure that appropriate interventions are put in place. These thresholds and actions are summarised in the table below. Fieldworkers will be responsible for identifying patients with dangerously high blood pressure, and for referring them back to the clinician on duty for emergency care. Fieldworkers will also refer participants who become visibly emotionally distressed in response to the mental health components of the questionnaire. Referral letters to clinic staff have been piloted, and are included in Appendix 4. All safety monitoring will be uniformly implemented across intervention and control clinics so as not to bias the trial.

**Table 4. Safety monitoring of participants**

| **Parameter** | **Risk** | **Responsible for identifying dangerously raised values and acting on these** | **Threshold for intervention** | **Intervention** |
| --- | --- | --- | --- | --- |
| Blood pressure | Acute cardiovascular event e.g. stroke | Fieldworkers | Systolic blood pressure ≥ 180mmHg  Diastolic blood pressure ≥ 110mmHg | Refer back to clinician for review using structured referral letter |
| Psychological distress | Suicide | Fieldworkers | Visibly emotionally distressed during interview with limited recovery by end or volunteered suicidal thoughts during interview. | Refer back to clinician for review using structured referral letter |
| Triglycerides | Pancreatitis | Independent safety officer | ≥15mmol/l | Independent safety officer to alert study manager who will notify clinic staff and direct appropriate intervention |

An independent Data and Safety Monitoring Board is not considered necessary because this is not a Phase III trial, and all interventions contained in the guideline are known to be beneficial in the management of chronic diseases. Furthermore, all treatments are currently available at intervention and control clinics. We are only randomising an intervention that seeks to optimise their provision and established care for chronic diseases at these clinics.

The trial will be registered with the South African Clinical Trials Register and www.controlled-trials.com.

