**Potential harms and measures to protect from harm**

The risks of these studies to the participants are minimal. The usual care will in no way be compromised if a patient chooses not to participate. Research procedures will take place after patients have received care at the clinic. The trial is not a Phase III trial where we are testing new treatments for chronic diseases but rather whether outcomes can be improved through the provision of a guideline-based training programme targeting nurses and doctors. The guideline is based on the best available evidence and is consistent with national recommendations. Care will be provided by experienced health practitioners. The Western Cape Department of Health will use the results of the trial to guide further implementation.

The following participants will be referred back to clinical staff for further assessment on the day of their interview (at baseline and follow up):

1. Participants with very high blood pressure (≥180/110) as they are at increased risk for stroke or heart attack.
2. Participants who become visibly emotionally distressed when answering the mental health component of the questionnaire

The following participants will be referred back to clinical staff for further assessment on the day of their interview at follow up only:

1. Participants with undiagnosed hypertension (blood pressure ≥140/90)
2. Participants who answer ‘yes’ to the following question, which has been added to the follow up questionnaire: Has the thought of ending your life been on your mind’.

An independent safety officer will review all blood results, and if safety thresholds are exceeded, contact clinic staff to ensure the participant is recalled, and action taken.

There is also minor risk of discomfort, bruising and bleeding during or after blood is drawn. This will be minimised by using only registered health practitioners to perform this procedure.

Confidentiality of data will be ensured by using computers for data entry. Once entered data may not be reviewed, and there are no paper questionnaires that could be lost or left in view of others. Uploaded questionnaires will be stored on a secure server. Access to identifiers will be restricted to a few key study staff for the purposes of data linkage with other datasets, and quality assurance. Only anonymised extracts will be prepared for analysis by study statisticians and researchers.

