The trial co-ordinator will recruit fieldworkers from local community networks, and preference will be given to those with experience in community based surveys. Excellent knowledge of the community will be a pre-requisite to help find participants who do not return to the clinic for follow-up interviews. Fieldworkers will undergo a three to five day training covering: enrolment procedures and consent, measurement of blood pressure and other parameters, use of the handheld computer and general clinic staff liaison and interviewing skills.

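### Table 4 sets a narrower trigger for psychological-distress referral than the Synopsis and the safety plan's own text, leaving out a calm yes at follow-up and distress that settles

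*Combined protocol and SAP*

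**What the plan says.** The rule for referring a participant back to clinic staff on mental-health grounds appears in four places.

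- **Synopsis, Potential harms and measures to protect from harm.** At baseline and follow-up it refers "Participants who become visibly emotionally distressed when answering the mental health component of the questionnaire". A second list opens "The following participants will be referred back to clinical staff for further assessment on the day of their interview at follow up only" and includes anyone who answers yes "to the following question, which has been added to the follow up questionnaire". The question asks about thoughts of ending one's life. Distress is not a condition.
- **Data safety and monitoring plan, text.** "Fieldworkers will also refer participants who become visibly emotionally distressed in response to the mental health components of the questionnaire". The next sentence reads "Referral letters to clinic staff have been piloted, and are included in Appendix 4". On thresholds in general it says "These thresholds and actions are summarised in the table below".
- **Table 4, psychological distress row.** The threshold is "Visibly emotionally distressed during interview with limited recovery by end or volunteered suicidal thoughts during interview", and the action is referral to the clinician with a structured letter. The row does not separate baseline from follow-up.
- **Appendix 4, combined letter.** This urgent letter, used at follow-up, gives visible distress, a yes to the question, or both, as the reason for referral.

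The section on potential risks and protection from risk names suicide among the risks that study procedures may bring to light. It sends the reader to Table 4 for management.

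**The concern.** Two places name Table 4 as the source for the safety thresholds and for managing suicide risk, yet its trigger is narrower than the referral rules elsewhere in the current text. The same interview can therefore end with or without a referral, depending on which section the fieldworker follows. The worst case is a participant who discloses suicidal thoughts calmly, in answer to the question, and goes home without being seen that day.

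The people applying the rule are fieldworkers recruited from community networks. The plan says "Fieldworkers will undergo a three to five day training covering: enrolment procedures and consent, measurement of blood pressure and other parameters", and goes on to use of the handheld computer, clinic liaison and interviewing skills. Neither distress nor suicide risk is named among the topics, so a clear written rule matters.

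**Working it through.** There is no figure to reproduce. The check sets the current texts side by side for the two situations in which they could differ.

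| Place | Visible distress that settles (either interview) | Calm yes (follow-up only) |
| --- | --- | --- |
| Synopsis, potential harms | Refer that day | Refer that day |
| Safety plan, text | Refer | Not stated; reached only through the pointer to Appendix 4 |
| Table 4 | Threshold not met | Threshold not met, if *volunteered* means unprompted |
| Appendix 4 combined letter (follow-up) | Printed as a reason for referral | Printed as a reason for referral |

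**Calm yes at follow-up.** The Synopsis makes the answer sufficient in itself. In Table 4, such a participant fails the distress limb. The other limb covers suicidal thoughts that are volunteered, which in ordinary usage means offered without being asked; a yes to a set question is not that. The safety plan's text names only distress. It leads to the trigger only because the letter it points to mentions it, and a fieldworker normally takes up a referral letter after deciding to refer.

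**Distress that settles.** The Synopsis and the safety plan's text refer visible distress without a recovery condition. Table 4 adds the condition that recovery be limited by the end. This conflict does not depend on how *volunteered* is read, and it lies within the safety section itself: the text and the table that summarises it disagree.

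**Scale.** Research procedures and data collection says that one questionnaire serves all trial participants, so the follow-up question is not confined to the depression cohort. The plan is for 4598 participants with a 20% allowance for loss. That gives about 4598 × 0.8 = 3678 follow-up interviews, or 4598 / 1.2 = 3832 if the allowance was applied as a multiplier. These are interviews that the rule governs, not missed referrals.

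**The case against.** The strongest reply is that the serious case is already covered. The Synopsis states the follow-up rule plainly, the letter in use at follow-up prints the trigger, and the safety plan's text points to that letter. Table 4 is called a summary and does not say that its triggers are the only ones. No section tells a fieldworker not to refer a calm yes. Fieldworkers are also supervised, with site visits during interviews.

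Much of this stands, and it rules out several stronger readings.

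- A reader might infer that the plan has no rule for disclosed suicidal thoughts at follow-up. It has one, in the Synopsis and in Appendix 4.
- A reader might infer that the whole safety section contradicts the Synopsis. On distress that settles, its text agrees with the Synopsis and only Table 4 differs. The text's gap is confined to the yes trigger.
- A reader might add a third conflict: suicidal thoughts volunteered at baseline without distress, which Table 4 refers and the other places do not name. That is silence, and the sections can be read together.
- A reader might infer that participants will be missed, or that the arms will be treated differently. The documents give no rate of yes answers, and the safety plan requires uniform monitoring across arms.

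The reply does not remove the mismatch. A table described as holding the thresholds, and cited for managing suicide risk, should not be narrower than the rule it summarises. Reading *volunteered* generously would rescue the calm yes but not the distress that settles.

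**Conclusion.** Table 4 is wrong as written: its psychological-distress threshold does not match the current referral rules. It omits the follow-up yes, and it adds a recovery condition that neither the Synopsis nor the safety plan's text contains. The first part rests on the ordinary meaning of *volunteered*; the second needs no assumption.

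This is a point of participant safety. No estimate, test, sample size or power figure is affected, and no count of missed referrals is claimed. It is worth correcting because the rule concerns suicide risk and the correction is small.

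The wording of the baseline letter, the absence from Table 4 of a row for undiagnosed hypertension, and the safety plan's appendix reference are not grounds for this finding.

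**What to change.** Reword the threshold in the psychological distress row of Table 4 so that it covers:

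- any visible emotional distress in the interview, whether or not it settles;
- any suicidal thoughts that the participant volunteers;
- at follow-up only, a yes to the suicidal-thoughts question, distressed or not.

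For the follow-up yes, state the action as same-day referral with the Appendix 4 letter. Add the same follow-up trigger to the text of the Data safety and monitoring plan.

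Putting the recovery condition into the Synopsis and the safety plan's text would also make the sections agree on distress. However, it would narrow a rule that both now state, and the yes trigger would still have to be added.

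The cost is a revised table row, one added sentence and a short fieldworker briefing. Referrals may rise in both arms if Table 4 has been the rule in practice. The follow-up triggers fire at the interview that records the outcome, so they leave the primary outcomes untouched. Because the depression outcome counts referral for counselling or to psychiatric services, extra baseline referrals could in principle feed into it. But baseline referral of visible distress is already required by the Synopsis and the safety plan's text. If baseline interviews are complete, only follow-up practice changes.

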## Data analysis

The University of Cape Town Lung Institute will take primary responsibility for storing the data in electronic format. Electronic data will be uploaded to a password-protected sub-directory of a secure server. This network server is backed up daily and will meet the requirements of security and confidentiality of the data. The research data sets will not contain any personal or identification information. A link to identification information will be through a unique study number assigned to participants. Only the data architect and study manager will have access to named datasets, for linkage and quality control purposes.

All protocols, questionnaires, other data sheets, correspondence relating the ethical clearance for the relevant studies and hard copies of study information will be kept in locked cupboards at the project office at the University of Cape Town.

Blood will be analyzed at a private laboratory, Pathcare, accredited with SANAS (South African National Accreditation System) according to ISO 15189 standards. This laboratory has always adhered to international guidelines with regard to:

- - - 1. Control of specimen processing and results distribution,
      2. Documentation of standard operating procedures,
      3. Maintenance of equipment,
      4. Adherence to accepted laboratory safety procedures,
      5. Rapid turn-around times, and
      6. Monitoring and verification of results generated.

The Laboratory also participates in an external quality assurance program, the international Bio-Rad (previously Murex) Clinical Chemistry Quality Assessment Program. Relevant performance ratings for the analyses being used can be provided if required.

Efforts to ensure the accuracy and reliability of the data include: training and supervision of fieldworkers, including site visits during recruitment and patient interviews; implementation of automated skips, required fields, and range checks on the handheld interview programme; and routine quality reports on the database.

Data analysis plans are specific to each of the three studies and have been described in the relevant sections.

Three sets of mortality data are available to study the mortality patterns in South Africa.

1. Statistics South Africa provide unidentified public domain data with underlying cause of death based on vital registration within about 2 years of the event. The lowest level of geographic information is province.

2. Identified (ID number) data is available from the population register within about 3 months of the event with limited information on whether cause is natural or external. This data is restricted to deceased who are registered.

3. The Western Cape Provincial Government has extended a local level mortality surveillance system from 2 health districts to cover the province as of 2008. This will provide underlying cause of death as well as health sub-district and will be identifiable with ID. It will also include deceased who are not registered.

All mortality data will be stored by the Medical Research Council in keeping with existing agreements with the Department of Home Affairs and the Western Cape Department of Health.

## Description of risks and benefits

### Potential risks and protection from risk

The risks of these studies to the participants are minimal. The trial is not a Phase III trial where we are testing new treatments for chronic diseases. Rather we are evaluating whether chronic disease care and outcomes can be improved through the provision of an integrated guideline-based training program targeting nurses and doctors, and there is equipoise as to whether patients in either arm would be at greater risk. The guideline is based on the best available evidence and is consistent with national recommendations. Care will be provided by experienced health practitioners. The effects of the proposed research will be to randomly allocate implementation, and to provide training, managerial support and evaluation to ensure optimal implementation.

Participants may be newly identified as being at risk for an acute cardiovascular event, pancreatitis or even suicide through study procedures, namely blood pressure, triglyceride measurement and administration of the mental health components of the questionnaire. Management of such participants is outlined in Table 4.

There is also minor risk of discomfort, bruising and bleeding during or after phlebotomy, but this will be minimised by using only registered health practitioners to perform this procedure. Participants will be seated and standard infection control procedures will be enforced. All samples will be handled using strict criteria for the management of bodily fluids, including use of special sharps containers, special hazardous waste disposal units, alcohol and bleach cleansing of surfaces, use of latex gloves by all personnel, and occlusive covering of all puncture sites.

The usual care of participants will in no way be compromised, or jeopardized if a patient refuses to participate. Research procedures will take place after patients have received care at the clinic.

### Significance and potential benefit of research to participants and others

The trial is opportunistic and is proposed alongside initial incremental implementation of the integrated guideline-based training program in the Western Cape. Potential benefits are therefore related to the provision of training, managerial support and evaluation to ensure optimal implementation in all 520 primary care facilities in the province.

In resource-restricted settings like Southern Africa, new programmes are introduced at an opportunity cost to other priorities. This brings with it an ethical imperative to commit to open minded development of interventions, followed by experimental field testing that draws reliable conclusions about effectiveness and allows for ineffective or even harmful interventions to be dropped without delay. Introducing the integrated guideline-based training programme within the context of a pragmatic randomised controlled trial means that two ethical imperatives at programme level are met. Firstly the need to ensure that rising demand for treatment is met - equity; and secondly the Department of Health mandate to implement innovation in the presence of careful evaluation to ensure maintenance and improvement of quality - responsible stewardship over resources and protection of the population from harm.

If the pragmatic trial shows that the programme is effective, it suggests that implementation in other resource-restricted settings in South Africa and in the region will yield positive results. Results of the trial could be used to inform decision-making at a national and regional level. Within the Western Cape, the plan is to integrate the programme, if effective, with a component targeting community health workers, currently under development.

##

## Informed consent

Trained fieldworkers will be responsible for the consent process. Patients 18 years or older will be invited to participate in the studies in the waiting room, and a plain language information sheet will be provided, allowing them time to consider and discuss possible participation. Interested patients will be screened after consultation with the clinician, and in privacy, in an area of the clinic temporarily allocated to research staff.

Consent will be conducted in the language of the participant, and fieldworkers will be recruited accordingly. The screening process includes the identification of participants with impaired capacity to consent, whether because of acute illness, a psychiatric condition or severe cognitive impairment. These patients will be excluded from the study, as the study requires that participants actively engage in an interviewing process at the time of recruitment, and 12-15 months later.

Potential participants will be warned that only highly abnormal blood results will be brought to the clinic’s attention. This is because routine monitoring of HbA1C and lipids comprises a key guideline recommendation, and thus component of the training intervention. If all results were routinely returned, abnormal values may prompt clinicians to alter treatment, and confound measurement of the training’s effectiveness. Participants will be asked their permission to access hospitalisation, laboratory and death records through linkage using their South African identity number, folder numbers, and other identifiers.

A copy of the English version of the patient information sheet/ consent form is provided in Appendix 6.

Permission to perform the trial is being sought from the Western Cape Department of Health. The Department will also be asked to provide consent for patient-level data on hospitalisations and laboratory tests, drawn from routine databases, to contribute to the analysis.

## Privacy and confidentiality

To protect confidentiality, a unique number will be assigned to each participant. The identity number will not be linked to names or telephone numbers, except in a log which will be kept locked in the trial co-ordinator office. Identifiers will be destroyed after the data are entered into the computer and the data collection process is complete. Thereafter the only list with patient identifiers will be securely stored at the study offices.

## Reimbursement

Trial participants will be entitled to a food voucher worth one hundred rand (R100) which they will receive on the day of the follow up visit to the clinic to compensate for their participation in the study. Participating patients will also be reimbursed transport expenses in the form of a standard fee. It is hoped that the voucher will serve to incentivise participants to return to the clinic for the follow-up interview. This is necessary because of the long period between enrollment and follow-up (12-15 months) needed to detect differences in chronic disease care, characterised by infrequent (3-6 monthly) clinical review. Participants who do not return to the clinic for their interview will be followed-up at home, and receive their voucher once the interview has been completed. Should the fieldwork team determine that the participant has died at follow-up, the voucher will be passed onto their family.

